#### **Statistical method:**

For the statistical analysis of the information gathered SPSS Statistics ( IBM Corp. Released 2020. IBM SPSS Statistics for Windows, Version 27.0. Armonk, NY: IBM Corp) will be used. The frequency, mean, and standard deviation or median and interquartile range will be calculated for the tested

variables. The data will be collected from the participants before and after starting the program.

The paired t-test will be used for within group comparisons while the unpaired will be used for the between group comparisons.

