### **Delimitation:**

The study will be delimited to:

1. Patients with plantar fasciitis of both genders
2. The age will be ranged from 20 to 50 years old.
3. The patients should be able to understand and follow the verbal instructions.
4. The pain should be from moderate to severe.
5. Functional limitation from moderate to severe

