### **Significance of the study:**

To provide evidence that both protocols are effectiveness but there is lacking in the previous literature about the difference between 2 protocols when using the shock wave when handling cases of PF.

Shockwave therapy is a safe and effective non-surgical treatment of plantar fasciitis comparing to other treatments. Moreover, the researchers recommend the use of shockwave therapy for plantar fasciitis.

This study may help physiotherapists to exclude using the slow acting devices and save the time by using a specific protocol of a fast effective modality in the treatment of PF.

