**Sample size estimation:**

A pilot study will be conducted to detect the effect size required (at alpha level of 0.05 and power of 0.8)

A priori power analysis will be performed (G\*power, version 3.1.9.3, Duesseldorf, Germany), based on previous studies on PF

Pain, considered the Primary outcome measure and revealing a visual analogue scale (VAS) of 4-10 on the pain scale for PF.

Function limitation considered the secondary outcome measure and exposing a Foot Function Index of 100/170 or at least 60%.

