#### Control group - C:

This group will receive the same physiotherapy program in addition to sham shock wave therapy

The pain and function improvement will be assessed before and after 6 sessions. An additional assessment will be performed at the end of the 12th week for a short follow-up

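### The protocol plans within-group paired t-tests without limiting them to description, and these tests cannot show that either shock wave protocol is effective

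*Protocol*

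**What the plan says.** Statistical method gives the inferential plan in one sentence: "The paired t-test will be used for within group comparisons", and the same sentence goes on to assign unpaired tests to comparisons between groups. It names no primary comparison and does not restrict the paired tests to description.

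Two other sections bear on how these tests might be read. Significance of the study opens with "To provide evidence that both protocols are effectiveness" and then turns to the lack of literature on how the two protocols differ. Outcomes, under Visual Analog Scale, presents the VAS before and after treatment as the way to gauge how effective treatment is. Trial design calls the study a pre-test post-test randomized trial.

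On patients and treatment, Delimitation says "The pain should be from moderate to severe", and Sample size estimation describes pain as VAS 4-10. Groups A and B receive a physiotherapy program plus shock wave. For group C, "This group will receive the same physiotherapy program in addition to sham shock wave therapy". The strengthening exercise section cites a study as showing that such exercises reduce pain in this condition.

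On size, the plan is still open: "A pilot study will be conducted to detect the effect size required" ("at alpha level of 0.05 and power of 0.8"), and "A priori power analysis will be performed". No number of patients, SD or expected change is stated.

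**The concern.** A paired t-test asks whether the mean change in one arm differs from zero. It has no comparator. In this trial a non-zero change is expected in every arm for reasons unrelated to shock wave: the common exercise program, natural course, placebo response and, because patients are chosen for substantial pain, regression to the mean. The sham arm exists to remove these, and a paired test makes no use of it.

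Since the protocol also speaks of showing that both protocols work and ties before-after VAS to effectiveness, a significant paired result in A and in B could be reported as evidence for each protocol. The text does nothing to prevent this. At stake is a conclusion of effectiveness that the data could produce even if shock wave added nothing to exercise.

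**Working it through.** The protocol states no figure to reproduce, so the check is an illustration under stated assumptions.

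**Assumed inputs** (none is in the protocol except alpha 0.05; two-sided testing is also assumed): VAS SD 2 cm at each visit; pre-post correlation r = 0.5, varied from 0.3 to 0.7; n = 10 to 30 per arm; no dropout; the same true mean change in A, B and C, i.e. no shock wave effect.

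**Formulas.** SD of change = SD × √(2(1 − r)) = 2 × √(2 × 0.5) = 2 cm. Noncentrality = (change / SD of change) × √n. Power is the probability that a noncentral t variable with n − 1 degrees of freedom exceeds the two-sided 5% limits. The arms are independent, so the probability that all three are significant is the cube.

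**At n = 20** (19 degrees of freedom, √20 = 4.472):

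- Change 1 cm: noncentrality 0.50 × 4.472 = 2.24; one arm 0.565; all three 0.565³ = 0.18.
- Change 1.5 cm: noncentrality 0.75 × 4.472 = 3.35; one arm 0.889; all three 0.889³ = 0.70.
- Change 2 cm: noncentrality 1.00 × 4.472 = 4.47; one arm 0.989; all three 0.989³ = 0.97.

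**Sensitivity to n** (r = 0.5; one arm / all three):

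| n per arm | 1 cm | 1.5 cm | 2 cm |
|---|---|---|---|
| 10 | 0.293 / 0.025 | 0.562 / 0.177 | 0.803 / 0.518 |
| 15 | 0.438 / 0.084 | 0.771 / 0.458 | 0.949 / 0.855 |
| 20 | 0.565 / 0.180 | 0.889 / 0.702 | 0.989 / 0.966 |
| 30 | 0.754 / 0.429 | 0.978 / 0.935 | 1.000 / 0.999 |

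**Sensitivity to correlation** (n = 20, change 1.5 cm): r = 0.3 gives 0.767 / 0.451; r = 0.7 gives 0.984 / 0.953. For a change of 0.5 cm, all three arms are significant at most 7% of the time over every n and r tried.

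**Regression to the mean.** If entry required VAS ≥ 4 and pain had mean μ and SD 2 before selection, the expected fall is (1 − r) × 2 × λ, where λ = φ(a)/(1 − Φ(a)) and a = (4 − μ)/2. For μ = 5, a = −0.5 and 2λ = 1.02, so the fall is 0.51 cm at r = 0.5 and 0.31 cm at r = 0.7. For μ from 4 to 6 and r from 0.5 to 0.7 the range is about 0.2 to 0.8 cm. The cut at 4 is taken from Sample size estimation; the Inclusion criteria list has no pain threshold.

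**The between-group test.** In 20,000 simulated trials per setting (r = 0.5, n = 15, 20 or 30, common change 1, 2 or 3 cm), the unpaired t-test on change scores for A vs B rejected in 4.9% to 5.2%, its nominal level.

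**Which arms exist.** Randomization & Allocation first speaks of two groups, then of three at 1:1:1 with C as control. The Control group - C section gives C sham. Data collection and Interventions refer to both groups, and the Extracorporeal shockwave therapy section gives the control group active shock wave. If only two active groups exist, the unpaired test compares one active protocol with another, and the paired test is the only one left that could be offered as evidence of effectiveness.

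**The case against.** The strongest reply is that the right test is already planned. The sentence on paired tests goes on to unpaired between-group tests, and the Statement of the problem, Purpose and Hypothesis all concern a difference between protocols, which the unpaired test addresses. With a sham arm, the between-group comparisons can include A vs C and B vs C. The phrase in Significance of the study is rationale, not an analysis rule, and the VAS paragraph assigns no test. A statistical analysis plan, not available here, may define the role of each test.

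Most of this stands, and it rules out three stronger readings:

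- A reader might infer that the paired tests are the planned tests of effect. Statistical method calls them only within-group comparisons; nothing says that a paired p-value decides efficacy.
- A reader might infer that the protocols will be compared by noting that one arm is significant and the other is not. That would be a serious error: at a 1 cm common change, identical arms disagree in 38% to 49% of simulated trials with 15 to 30 per arm. But no section plans it.
- A reader might infer that the paired tests will usually be significant in every arm, sham included. That depends wholly on assumed inputs: all three arms are significant in 18% of trials at 1 cm with 20 per arm, and in 97% at 2 cm. Regression to the mean alone is too small to produce it at these sizes.

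What the reply does not answer is that the protocol itself commits to paired tests, places them beside language about effectiveness, and leaves the sham arm in doubt.

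**Conclusion.** The point holds in limited form. The protocol does not rely on paired tests to compare the two protocols, and its between-group tests are suited to that question. It does plan within-group significance tests with no stated role, in a setting where they cannot separate shock wave from everything else that changes over six weeks. With no shock wave effect, 20 per arm and an SD of change of 2 cm, a single arm reaches significance with probability 57% to 99% as the common change goes from 1 to 2 cm. The reasoning does not depend on those figures, but their size does depend on inputs that the protocol leaves open. This is a cheap improvement to make before data are seen. It becomes more important if the two-group description is the true one.

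**What to change.** In Statistical method, replace the paired t-tests with within-arm mean change and 95% CI, labelled as description only. State that a conclusion that a protocol is effective rests on A vs C and B vs C, and that a conclusion that the protocols differ rests on A vs B, using the between-group comparisons already planned.

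Reconcile the two-group and three-group descriptions in Randomization & Allocation, Control group - C, Data collection, Interventions and Extracorporeal shockwave therapy. If it turns out that there is no sham arm, make no claim that either protocol is effective, and align Significance of the study with that.

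The cost is wording, and the loss of the within-group p-values. No extra patients or measurements are needed for this change.

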### **Randomization & Allocation**

In this study, patients will be randomly divided into two groups of equal number.

Restricted randomized sampling will be used in this study for randomization of the participants into three groups. Using permuted block randomization, with 1:1:1 allocation ratio. In a three group design, Blocks having equal numbers of As, Bs and Cs (A = intervention 1 and B = intervention 2, and C= control) are used, with the order of treatments within the block being randomly permuted

The groups will be:

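### The only between-group test named is a two-group t-test, but the allocation text randomises to three arms, with no primary contrast and no stated use of the baseline scores.

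*Protocol*

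**What the plan says.** The protocol's Statistical method section gives the inferential plan in one sentence: paired t-tests within groups, while "the unpaired will be used for the between group comparisons". It does not say which pairs of groups are compared, or whether the compared variable is the post-treatment score or the change from baseline.

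The Randomization & Allocation section states: "Restricted randomized sampling will be used in this study for randomization of the participants into three groups". It adds "Using permuted block randomization, with 1:1:1 allocation ratio". The group descriptions that follow define intervention A, intervention B and a sham control C. The same allocation section, however, opens by saying that "patients will be randomly divided into two groups of equal number". The Data collection section, the Interventions section and its shockwave (ESWT) part also speak of both groups, as if there were two.

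The Sample size estimation section sets the error rate ("at alpha level of 0.05 and power of 0.8") and ranks pain on the VAS as primary and function on the FFI as secondary. Sidedness, sample size, effect size and standard deviation are not given. The Hypothesis section expects a difference between shockwave protocols without naming a contrast, while the title and the Statement of the problem ask about two protocols. Pain and function are both measured before treatment. Post-baseline assessments are listed after 3 and after 6 sessions (Data collection) and at week 12 (Control group - C).

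**The concern.** A two-sample test cannot analyse three arms in one step. It has to be repeated over pairs, and the reader cannot tell which pairs or which of them decides the trial. With three arms there are three possible pairs. If each is tested at 0.05, the chance of at least one false claim exceeds the 5% that the protocol states. An investigator could also choose the pair to emphasise after seeing the results.

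The second issue is precision. Every participant has a baseline VAS and FFI, but no baseline-adjusted comparison is named and the analysed variable is left open. Post scores, change scores and baseline-adjusted scores can give different intervals and different p-values from the same data. Leaving this open adds another choice that can be made late.

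**Working it through.** The protocol states no family-wise error and no sample size, so there is no figure of its own to reproduce.

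**Inputs from the protocol:** alpha 0.05; three arms with equal allocation ("with 1:1:1 allocation ratio"); unpaired t-test between groups; VAS primary; three post-baseline times.

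**Assumptions, not in the protocol:** two-sided tests; baseline-outcome correlation r; for the power illustration, 26 per arm and a standardised difference d = 0.8.

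**1. Family-wise error, one outcome at one time, no true differences**

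- All three pairs: the largest of the three differences decides. In large samples the error is P(q > 1.96 × √2), where q is the studentized range of 3 means. This gives 0.1223, or 12.2%. Simulation of separate t-tests, 200,000 runs each at 10 to 100 per arm, gives 12.2% to 12.3%.
- A–C and B–C only: the two statistics share arm C and have correlation 0.5. The error is about 9.1%.
- A–B only: 5%.
- Upper bounds for three tests: 1 − 0.95³ = 14.3% if independent, and 3 × 0.05 = 15% by summing.

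**2. VAS at several time points, all three pairs, any significant result counted**

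Simulated at an assumed 30 per arm, with correlation between times falling from 0.7 to 0.3:

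- two times: 19.6% to 22.4%
- three times: 25.0% to 30.7%

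**3. Baseline adjustment**

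Take the variance of the post-score comparison as 1 and assume equal variance before and after treatment. A change score then has variance 2(1 − r), and ANCOVA has 1 − r² (ignoring the degree of freedom it spends). The ratio of ANCOVA to change score is (1 − r²) / (2(1 − r)) = (1 + r)/2.

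| assumed r | post score | change score | ANCOVA | ANCOVA ÷ change |
|---|---|---|---|---|
| 0.3 | 1 | 1.40 | 0.91 | 0.65 |
| 0.5 | 1 | 1.00 | 0.75 | 0.75 |
| 0.6 | 1 | 0.80 | 0.64 | 0.80 |

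ANCOVA therefore cuts the variance by 9%, 25% or 36% relative to post scores. Its variance is also below that of change scores at each of these correlations.

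**4. Power illustration (assumed 26 per arm, d = 0.8, two-sided 0.05)**

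A post-score t-test has 81% power. With ANCOVA the effective difference is d/√(1 − r²), which is 0.839, 0.924 or 1.000. Power becomes 84%, 90% or 94%.

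**5. Whether to place a global test in front of A–B**

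With three arms, a global test followed by unadjusted pairwise tests does hold 5%. At the same assumed values, requiring the 2-df test to be significant first lowers A–B power from 81% to about 71% if C lies midway between A and B, and to about 77% if C equals the worse arm. There is almost no loss if C is clearly worst. Naming A–B as the primary contrast avoids this cost.

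**The case against.** The strongest objection is that the number of arms is itself contradicted. Much of the protocol reads as a two-group trial. The shockwave part of the Interventions section even gives the control group active settings, whereas the Control group - C section gives it sham. Under a two-group reading the unpaired t-test is suitable and there is no pairwise inflation. This stands, so the contradiction must be settled first. It does not rescue the current text, because the detailed allocation scheme has three arms and the test sentence does not match it.

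A reader might infer that the plan inevitably produces a false-positive rate of 12% or more. The documents do not support that. Each single t-test keeps its 5%. The 12.2% needs all three pairs to be tested and any one result to count as success. If only A–B is confirmatory, as the title and the Statement of the problem suggest, the rate is 5%. Nor should VAS and FFI be pooled into one larger figure, since the protocol already ranks FFI as secondary.

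A reader might also infer that the baseline is thrown away. That is not established, because an unpaired t-test on change scores uses it. What can be said is that the analysed variable is not fixed. Under randomisation the unadjusted test is also valid, so ANCOVA is a gain in precision and not a repair of bias.

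Finally, a multiplicity rule or covariate list may sit in a statistical analysis plan that is not shown. Their absence from the protocol is therefore not the point. The point is that the protocol names a specific test that does not fit the design it describes.

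**Conclusion.** The point holds in a conditional form. The named two-group test does not match the three-arm allocation, and no primary contrast is named. The family-wise error for VAS at one time point is about 12.2% for all three pairs, about 9.1% for the two comparisons with sham, and 5% for A–B alone. It is higher if several time points are also tested without a rule. These rates assume two-sided tests, equal arms, no true differences and any significant result counted as success. They hardly depend on arm size.

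The baseline part stands whether there are two or three arms. The compared variable is unspecified, and a baseline-adjusted model would use data already collected. Its size depends on the assumed correlation: a 9% to 36% cut in variance relative to post scores for r from 0.3 to 0.6. The power figures are illustrations only, since the protocol gives neither a sample size nor an effect size.

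**What to change.** 1. Reconcile the two-group wording (Randomization & Allocation, Data collection, Interventions and its shockwave part) with the three-arm wording, including what the control group receives. The sponsor must decide which description is correct.
2. If there are three arms, replace the unpaired t-test with one ANCOVA of VAS after session 6 on arm, with baseline VAS as covariate. Report adjusted differences with 95% confidence intervals.
3. Name A minus B as the single primary contrast at two-sided 0.05. This matches the title and the Statement of the problem.
4. Make A–C and B–C secondary with a Holm adjustment: the smaller p-value is tested at 0.025 and, if significant, the larger at 0.05. This controls error within the sham pair. If the sponsor wants 5% across all three claims, the sham pair should be tested only after A–B is significant.
5. Analyse FFI the same way as secondary, and treat the other time points as supportive.

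If the trial proves to have two arms, steps 3 and 4 reduce to the one contrast, and the ANCOVA remains.

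The statistical text needs only a few sentences, no extra data, and the SPSS version already named. Settling the number of arms takes more work because it touches several sections. The small downside is that comparisons with sham face a stricter threshold.

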### **Interventions:**

Regular physiotherapy program to be introduced to both groups:

#### The stretching exercise program:

The program will consist of plantar fascia, gastrocnemius and soleus muscles. The stretching exercise for all these tissues will be in standing position front the wall then let the patient to move the painful feet back of the normal feet, and front knee slightly flexed. The therapist will ask the patient to keep the trunk and knee straight and stabilize the heel on the floor then lean toward the wall till feel the stretch all along the calf of the painful feet and hold the stretch for 20 to 30 seconds. This stretching exercises will done 5 times for 5 set per a day for 6 weeks (**Garrett TR et al, 2013**).

#### The strengthening exercise program:

The program will consist of a toe curl exercises, Marble pickup exercises, small ball roll exercises and heel raise exercises. The toe curl, marble pickup and small ball roll exercises will be instructed to the patients to sit comfortably on the chair with both feet on the floor, hence with toe curl exercises the therapist will put a small towel or tissue on the floor front the painful feet then the patients scrunch the toes to pull the towel or tissue toward them. The marble pickup exercises, the therapist will place 10 marbles and small box front the patient's feet and ask the patient to pick up one marble by using the toes and place it in the small box. A small ball roll exercises, the therapist will place small ball (tennis ball) front the patient's feet and ask the patient to roll it around for 2 minutes. The heel raise exercises will be instructed to the patient by ask the patient to stand front the wall with both feet on the floor then raise both heels so the patient will standing on the toes, if need support to do the exercises let the patient to stead on the wall with two hands. All these exercises will apply it 5 times in 5 set per a day for 6 weeks. This study showed that the effectiveness of strengthening exercises in reducing the pain with plantar fasciitis patients (**Thong-On et al, 2019**).

### Extracorporeal shockwave therapy (ESWT):

Extracorporeal shockwave therapy (physiotur) with Handpiece 12 mm will be set for the study group with the continues mode, frequency 15 Hz on heel, pressure of 3 and impulses of 1600. On the other hand, the parameter for controlled group will be set with frequency 10 Hz on heel, pressure of 4 and impulses of 800. Then apply it to the patients on painful area of the heel at different points (center and medial aspect of the heel) and will apply 200 impulses in each painful points till complete 1600 impulses with patients in the study group and 800 impulses with patients in the control group. The patients will be on prone position with rest both legs on the sigmoid wedge.

The program of strengthening and stretching exercises will be same for both groups combined with shockwave therapy but with different parameter in each group. Both groups will receive the intervention six times ( one time per week over two months) and will follow with home exercises program.

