#### Intervention group A:

The patients in this group will receive selected physical therapy program combined with shockwave therapy (ESWT) of these parameters :

1. Frequency : ( 15 Hz ) on heel
2. Intensity / pressure: 3
3. Impulses 1800
4. Number of Sessions : 6 session (1 per week)

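### The two shock wave protocols under comparison have conflicting impulse counts, and the 10 Hz arm is called control although control is sham

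*Protocol*

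**What the plan says.** Settings for the active arms appear in two places in Chapter III of the Protocol.

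- **Arm descriptions.** Intervention group A is set at "Frequency : ( 15 Hz ) on heel", pressure 3, "Impulses 1800", for six weekly sessions. Intervention group B is set at 10 Hz, pressure 4, with the same 1800 impulses and six weekly sessions.
- **ESWT section under Interventions.** The study group is set at "frequency 15 Hz on heel, pressure of 3 and impulses of 1600". For the other group, "the parameter for controlled group will be set with frequency 10 Hz on heel, pressure of 4 and impulses of 800". The section then repeats both counts as the stopping rule: 200 impulses at each painful point "till complete 1600 impulses with patients in the study group and 800 impulses with patients in the control group".

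The control arm is also described in two ways. Randomization & Allocation codes the arms as "A = intervention 1 and B = intervention 2, and C= control", and the Control group - C section says "This group will receive the same physiotherapy program in addition to sham shock wave therapy". The ESWT section describes only two groups, both given active shock waves, and does not mention sham.

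**The concern.** The statement of the problem, the purpose and the hypothesis all frame the trial as a comparison of two shock wave protocols. Each protocol is a package of settings: frequency, pressure, impulses and sessions. The introduction faults earlier studies for not fixing these parameters.

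If the impulse count is not fixed, the A versus B contrast is not one defined experiment. With 1800 impulses in both arms, A and B differ only in frequency and pressure. With 1600 against 800, they also differ twofold in impulses, so any difference in pain or function is mixed with the number of impulses. If therapists follow different sections, or the version is chosen after the fact, a reported difference may not be attributable to either package.

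The label adds a second, smaller risk. Someone setting up treatment from the ESWT section alone would give active 10 Hz shock waves to patients called control, which would undermine the sham comparison.

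**Working it through.** **Matching the arms.** The ESWT section does not use the labels A and B, but its frequency and pressure pairs identify them.

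| | Frequency, pressure | Impulses, arm descriptions | Impulses, ESWT section | Label in ESWT section |
|---|---|---|---|---|
| A | 15 Hz, 3 | 1800 | 1600 | study group |
| B | 10 Hz, 4 | 1800 | 800 | control group |
| C | sham | none given | not mentioned | none |

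Frequency and pressure agree across the two texts. Impulse counts and the control label do not.

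**Is it a slip?** The counts 1600 and 800 each appear twice in the ESWT section, first as a setting and then as a stopping rule, so a single typing error is unlikely.

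**Can the rule of 200 impulses per point decide?** No, because all three counts are multiples of 200: 1800/200 = 9, 1600/200 = 8, 800/200 = 4. These are numbers of 200-impulse applications, not of distinct heel points. The section names only the centre and medial side of the heel and does not rule out returning to a point.

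**Size of the conflict.** The impulse figures are read as per session, which is the natural reading but is not stated in the arm descriptions.

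- 15 Hz arm: 1600/1800 = 0.889, or 11% fewer.
- 10 Hz arm: 800/1800 = 0.444, or 56% fewer.
- A:B ratio: 1800:1800 = 1:1, or 1600:800 = 2:1.
- Course totals over six sessions: 6 × 1800 = 10,800 in each arm, or 6 × 1600 = 9,600 against 6 × 800 = 4,800.

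**Which arm gets more treatment?** On impulse count alone the order does not reverse; a tie becomes 2:1. The protocol defines no dose measure and gives pressure no unit, so the following are illustrations under assumptions.

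- Dose as delivery time (impulses/frequency): arm descriptions, A 1800/15 = 120 s and B 1800/10 = 180 s; ESWT section, A 1600/15 = 107 s and B 800/10 = 80 s.
- Dose as pressure × impulses: arm descriptions, A 3 × 1800 = 5400 and B 4 × 1800 = 7200, B/A = 1.33; ESWT section, A 3 × 1600 = 4800 and B 4 × 800 = 3200, B/A = 0.67.

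Under either measure, the arm with the larger dose switches between the two texts. This depends on the measure. With dose as pressure^k × impulses, B/A is (4/3)^k in the arm descriptions and 0.5 × (4/3)^k in the ESWT section. The switch therefore needs 0 < k < ln 2/ln(4/3) = 2.41.

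**The case against.** The strongest reply is that the ESWT section looks like a remnant of a two-arm plan and that the arm descriptions should prevail. Two-group wording also appears in Randomization & Allocation, in Data collection and at the start of Interventions, so the section's two groups reflect a wider inconsistency about the number of arms. However, no text gives the arm descriptions precedence. The ESWT section is also the only place that states the handpiece, mode, heel sites, impulses per point and patient position, so a therapist has to use it and will find 1600 and 800 there.

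A second reply concerns consequence. If a single centre applied one version consistently and reported it, the result would belong to that version. This is fair: the fault is that the package is not uniquely fixed in advance, not that every result would be uninterpretable. Nothing in the protocol makes consistent use of one version likely.

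Third, a reader of the whole protocol can resolve the control label, because the frequency and pressure identify arm B and the Control group - C section is plain about sham. This stands, and the label conflict is secondary. The impulse conflict cannot be resolved in the same way.

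Finally, the dose measures above come from this review and not from the protocol. That also stands, and the conclusion does not rest on them.

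**Conclusion.** The concern holds. The protocol contradicts itself on the treatment it sets out to compare, and nothing in it reconciles the two versions. The discrepancy is 11% of the impulses in the 15 Hz arm and 56% in the 10 Hz arm, and the ratio between arms moves from 1:1 to 2:1. These figures need only the match on frequency and pressure, which is exact. The course totals also assume that the counts are per session. The use of control for an active arm is a further, lesser error. Intervention settings belong in the protocol, so a separate statistical analysis plan would not be expected to resolve this. It must be corrected before treatment starts.

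**What to change.** Before the first treatment, the investigators should decide which impulse counts are intended; the document does not show which are right. Then:

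1. Put one table of settings for arms A, B and sham C in the protocol: frequency, pressure with its unit, impulses per session, number of heel points, number of sessions and interval. Include what the sham consists of.
2. Correct the Intervention group A, Intervention group B and ESWT sections to agree with that table.
3. Replace the study group and control group labels in the ESWT section with A, B and C, and reserve control for the sham arm.
4. As a side correction, the ESWT section says "Both groups will receive the intervention six times ( one time per week over two months". All sections agree on six weekly sessions, so state the span that follows from that schedule.

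Relabelling the ESWT section will not by itself remove the two-group wording elsewhere in the protocol, which should be corrected in the same amendment. The cost is amendment wording only if this is done before the first treatment.
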